## Abstract

**Introduction:**

There is a growing emphasis on improving primary healthcare (PHC) services and granting frontline service providers more decision-making autonomy. In October 2023, Kenya enacted legislation mandating nationwide facility autonomy. There is limited understanding of the effects of health facility autonomy on PHC facilities performance. It is recognised that stakeholder interests influence reforms, and gender plays a critical role in access to health and its outcomes. This protocol outlines the methods for a study that plans to evaluate the effects, implementation experience, political economy and gendered effects of health facility autonomy reforms in Kenya.

**Methods and analysis:**

The research will use a before-and-after quasi-experimental study design to measure the effects of the reform on service readiness and service utilisation and a cross-sectional qualitative study to explore the implementation experience, political economy and gendered effects of these reforms. Data to measure the effects of autonomy will be collected from a sample of 80 health facilities and 1600 clients per study arm. Qualitative interviews will involve approximately 83 facility managers and policymakers at the county level, distributed across intervening (36) and planning to intervene (36) counties. Additionally, 11 interviews will be conducted at the national level with representatives from the Ministry of Health, the National Treasury, the Controller of Budget, the Council of Governors, the Auditor General and development partners. Given the uncertainty surrounding the implementation of the reforms, this study proposes two secondary designs in the event our primary design is not feasible—a cross-sectional study and a quasi-experimental interrupted time series design. The study will use a difference-in-difference analysis for the quantitative component to evaluate the effects of the reforms, while using thematic analysis for the qualitative component to evaluate the political economy and the implementation experience of the reforms.

**Ethics and dissemination:**

This study was approved by the Kenya Medical Research Institute Scientific and Ethics Review Unit (KEMRI/SERU/CGMR-C/294/4708) and the National Commission for Science, Technology and Innovation (NACOSTI/P/23/28111). We plan to disseminate the findings through publications, policy briefs and dissemination workshops.

WHAT IS ALREADY KNOWN ON THIS TOPICExisting evidence from high-income countries suggests that hospital autonomy has positive effects on service delivery.WHAT THIS STUDY ADDSThis study contributes by examining health facility autonomy at the primary healthcare level in a lower-middle-income country with semiautonomous subnational governments.HOW THIS STUDY MIGHT AFFECT RESEARCH, PRACTICE OR POLICYOn completion, this study will enhance our understanding of empowering frontline facility managers to make informed decisions, potentially influencing future research, healthcare practices and patient experience.

## Background

 Primary healthcare (PHC) is an entire society’s approach to delivering timely, comprehensive and people-centred health services as close as possible to people’s everyday surroundings.^1^ PHC prioritises the delivery of essential health promotion and disease prevention, in addition to treatment, rehabilitation and palliative care, and is a crucial element in universal health coverage as it ensures equitable and efficient access to healthcare that prioritises the needs of individuals.^2^ First referral hospitals and peripheral outpatient health facilities are integral in delivering facility-based PHC services in low-income and middle-income countries (LMICs). Evidence shows that how health facilities are organised and managed determines their effectiveness and the extent to which they meet service delivery goals.^1 3^

Health facility autonomy is a crucial aspect of the organisational structure and management of health facilities. Health facility autonomy refers to the level of control and influence that health facilities have over key functions health facility administration, financial management, procurement, human resource management and strategic management.^4^ Historically, health facility autonomy reforms emerged as part of new public management prescriptions for hospital reforms and entailed both decentralisation of functions to hospitals and exposure to the market.^5^ The level of autonomy granted to public facilities has been shown to directly affect their performance.^2^ Unfortunately, in LMICs, most public PHC facilities lack autonomy over most of the managerial functions. For instance, less than 40% of facilities in LMICs have autonomy to retain and spend their revenue.^2^

Historically, health facility autonomy reforms have been introduced to enhance the efficiency of health facility operations and reduce their reliance on government budgets. Autonomy reforms have also been part of broader decentralisation reforms aimed at improved efficiency and equity of health systems as well as enhance local participation and accountability.^46^,^8^

However, like broader decentralisation reforms, there is mixed evidence regarding whether granting PHC facilities autonomy improves health facility performance in LMICs. For example, a study conducted in India found no significant relationship between health facility decision-making autonomy and performance.^9^ In Uganda, a study that explored the health facility decision space found increased autonomy to be positively associated with the availability of drugs but negatively associated with quality of care and performance management.^10^ In Tanzania, increased autonomy has had varying levels of effects on performance, linked to the functionality of the facility governance committees.^11^ The mixed evidence may be attributed to context-specific factors influencing the effects on autonomy.^12^ These mixed findings notwithstanding, there is increasing attention to leveraging health facility autonomy to improve the performance of health facilities and to enhance the role of the people in health service delivery, more so in PHC facilities. In addition, often health system reforms are experienced differently across genders, it is important that policy reforms consider the gendered impact to mitigate for unintended consequences.

Methodologically, most studies that have documented the effects of autonomy reforms have been qualitative^4 7 8 13^ and the few quantitative studies in this area are cross-sectional, presenting attribution challenges.^9^ This study proposes to adopt a mixed methods approach, incorporating a qualitative inquiry, and a range of quantitative methods (quasi-experimental before and after, cross-sectional and interrupted time series (ITS) designs) aimed at estimating the effect of autonomy reforms. The study also proposes to conduct a political economy and gender analysis of autonomy reforms, both of which have not been examined in previous studies of autonomy.

### Autonomy reforms in Kenya

Kenya has been on a path to improve service delivery through devolution and more recently increased investments in PHC services.^14^ Kenya devolved health service delivery to county governments in 2013. Health facilities enjoyed some level of autonomy before devolution (health facility administration, financial management, procurement, human resource management and strategic management), through the health management services fund for hospitals and health sector services fund for health centres and dispensaries, which was shown to be effective in enhancing service delivery.^13^ However, following the devolution of health services in 2013, health service delivery was reorganised with county health management teams (CHMTs) taking up the responsibility for the management of health services and usurping the autonomy of subcounty and facility management committees.^7^

Over time, various counties have acknowledged the need for facility managerial autonomy and have allowed facilities some level of financial and procurement autonomy.^15^ Across these counties, this has been done through various means including enactment of county-level legislation and/or adoption of county-level policies to facilitate health facility autonomy. However, many counties have continued to limit the autonomy of health facilities. At the time of writing this protocol, the country had recently enacted a new Facility Improvement Funds (FIF) law that aimed at according some level of financial and procurement autonomy to public sector health facilities across the country.^16^ The law requires that facilities in the country are allowed to retain and spend their own source revenue. This law mandates all counties to implement autonomy reforms. However, the government was yet to establish guidelines for the implementation of this new law. Furthermore, due to the devolution of the management of health services in the country, the adoption and implementation of this new law is likely to depend on individual county leadership, unlike before the devolution when national laws were adopted exactly as guided by the national government. This will likely lead to variations in uptake of facility autonomy across counties in terms of both time of implementation and mechanism of implementation. These variations in implementation provides an opportunity to evaluate the effectiveness and implementation experience of autonomy reforms.

In addition, it is crucial to consider the gendered effect of these autonomy reforms. Within Kenya, and in other African countries, there is a gendered influence in health leadership progression, with women often lagging.^17 18^ In Kenya, it has also been shown that policies that are gender sensitive have had a positive influence on women in leadership.^17^ It is important to assess whether the autonomy reforms will reflect the representation of women in decision-making. In addition, gender dynamics often play a significant role in healthcare utilisation, access and outcomes.^19 20^ This study will explore whether the autonomy reforms have differential effects on men and women, considering factors such as health system leadership positions, access to services, health outcomes and the involvement of women in decision-making processes at the community and facility levels. Addressing gender-specific challenges and opportunities within the framework of PHC and facility autonomy will contribute to a more comprehensive and inclusive understanding of the healthcare system in Kenya.

It is important to document these autonomy reforms, their successes and failures, to provide learning points for counties willing to implement similar reforms in the future and for other LMICs keen on enhancing PHC provider autonomy. This study seeks to examine the effects, implementation experience, political economy and gendered effect of facility autonomy reforms among counties in Kenya.

## Methods

To address the above objectives, this study will adopt a concurrent mixed-method study design. The quantitative component of the study will entail a before and after quasi-experimental study as the primary design. The qualitative study will entail (1) a process evaluation and (2) a political economy analysis (PEA) of the facility autonomy reforms. Both the quantitative and qualitative elements of the study will incorporate a gender lens. This study started in January 2023 and will end in February 2026.

### Evaluation framework: theory of change (ToC)

This study will be guided by a ToC (figure 1) which we developed from reviewing literature on the relationship between facility autonomy and facility performance and a co-creation workshop that brought together 25 health sector stakeholders drawn from the national and county level and government and development partners. The ToC assumes that facility autonomy spans key functions of the facility including strategic management, financial, procurement, human resource management and facility administration.^7^ This autonomy will require effective legislation, a favourable political environment, facility managerial capacity, facility capacity to claim reimbursements, facility governance structures, increased facility decision space, complementary funding from counties, roll-out of financial management information system to facility level and established accountability mechanisms.^4^ The key activities will include training to management, specification of actor roles, functional facility boards and committees, functional health management committees, setting measurable targets, delegation of authority to the facility management teams, establishment of facilities as procurement entities, county oversight - approval of Authority to Incur Expenditure, supportive supervision by the county and sub-CHMTs, integration of facility and county planning, subsidisation of the cost of care for the poor to guard against inequity, generation of performance data and mobilisation of funds.^47 21^,^23^

**Figure 1 F1:**
[figure not shown]
Theory of change. PHC, primary healthcare.

The immediate outputs expected from the inputs and activities include timely decision-making, enhanced community participation in facility,^7 24 25^ effective management of staff,^24 25^ reduced bureaucracies in procurement and recruitment, increased community awareness of services implementation of planned activities,^7 26^ increased access and use of facility funds,^7 26^ enhanced predictability on financing,^4^ timely payment of salaries,^4 26^ timely procurement^4 26^ and, finally, effective planning for services.

The expected medium-term outcomes include increased budget responsiveness to needs, enhanced resource mobilisation, increased retention of managers, improved staffing, increased staff motivation,^7 26 27^ reduced absenteeism, increased Human Resources for Health (HRH) productivity,^4 24 25^ improved availability of basic services, reduced stockout of essential medicines, cost consciousness, improved reporting, improved citizen accountability and participation, improved facility management and ordering of medicines and supplies based on need. These medium-term goals should then result in the achievement of the following long-term goals: improved access to services, improved quality of services, enhanced facility efficiency, improved sustainable PHC financing, improved accountability, increased client satisfaction, increased service demand/utilisation and efficient referrals.^4 7 26 27^

From the literature, the effect of autonomy reforms is subject to context which is determined by institutional, socioeconomic and geographic factors.^12^ As such, we will monitor constraints that are likely to influence the effectiveness of the reform including weak legislation, dysfunctional boards/committees, limited decision space, political pressures, cash disbursement delays and poor preparation/training.^4 8^

Finally, autonomy reforms may have unintended negative consequences including increased cost of services, misappropriation of funds, ignoring basic services that do not generate revenue, over-reliance on user fees, reshaping quality based on ability to pay, lower quality of goods and services, increased facility debts and increased out of pocket payments. We will monitor the possible unintended consequences and document the efforts by counties to mitigate them.

### Evaluating the effects of autonomy reforms

#### Primary study design

We will employ a before and after quasi-experimental study to measure the effects of health facility autonomy on health facility readiness, functionality, service utilisation and client satisfaction of health facility autonomy reforms. We will conduct an assessment before implementation of the FIF reforms and an assessment after 12 months of implementation of the FIF reforms. The primary outcome of interest will be health facility readiness.

#### Secondary study design

There are uncertainties about the roll-out of autonomy, with possibilities that might compromise the proposed study design (quasi-experimental before and after design). The pace of autonomy reforms roll-out could be slow, with the implication that the selected intervention counties do not convert to intervention counties (ie, autonomy reforms are not implemented in these counties over the 12-month study period). To mitigate this, we will sample four additional intervention counties that have already implemented autonomy reforms. We will use a cross-sectional study design comparing these four counties that are already implementing autonomy, with the counties that do not have autonomy (control counties). This design will also ensure that we can measure effects in the event the time of the study is not sufficient to measure effects within counties that are just rolling out autonomy.

Further, we will use an ITS design to evaluate the effects of the reforms in the counties that will have rolled out the reforms across the country. We will collect and analyse monthly District Health Information System (DHIS) data on key performance indicators from PHC facilities across selected counties in Kenya, spanning 24 months before the introduction of autonomy reforms in a county and 24 months after its introduction. Exact times for pre-intervention and post-intervention phases will vary based on the exact time that autonomy reforms were introduced in a county.

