#### Study population

We intend to assess selected counties, selected facilities and clients receiving services from the selected facilities. For the county assessment, the study population will be the 47 counties from which we have selected 12 counties—4 implementing autonomy reforms, 4 planning to implement and 4 controls. For the facility assessment, the study population will be all county-owned public facilities within the selected counties across all level 2-6 of service provision level 2 (dispensaries), level 3 (health centers) level 4, 5 and 6 (hospitals) (table 1). Level 1 in Kenya comprises community health services, these will be excluded as at the time of the protocol, there were minimal to no mechanisms for payment for services provided at that level. For the client exit interviews, the study population will be all patients or carers whose patients had received services from the selected facilities on the day and time of the survey. These will include patients or carers seeking services such as outpatient services, antenatal services, postnatal services, child welfare services, management of chronic illness and maternity services and those discharged from inpatient care.

**Table 1 T1:** Selected counties with distribution of facilities

Group	County	Level 2	Level 3	Level 4	Level 5	Level 6	Total facilities in county
Controls	Tana River	44	5	3	0	0	52
	Migori	115	19	14	0	0	148
	Embu	88	9	4	1	0	102
	Kirinyaga	47	22	4	0	0	73
Already implementing	Makueni	189	39	12	0	0	240
	Mombasa	40	8	4	1	0	53
	Nakuru	140	26	17	1	0	184
	Kajiado	81	21	5	0	0	107
Intervention	Kakamega	111	48	12	1	0	172
	Lamu	29	3	3	0	0	35
	Homabay	120	48	16	0	0	184
	Nyandarua	54	24	2	0	0	80
	Total by level	1058	272	96	4	0	1430

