#### Sample size and sampling

There will be three levels of sampling for this study. The first level is county sampling, where we will purposively sample four counties already implementing autonomy reforms, four planning to implement the intervention and four not implementing as control. From the sampled counties, we will randomly sample 80 health facilities per group, assuming a mean difference of 10% in facility readiness between the two groups and a population variance of 400 across the groups using 80% power, 95% confidence level and a design effect of 1.2. Because the autonomy reforms have the biggest effects on facilities that raise revenue, we will sample all facilities from levels 4–6 from the selected counties. Leve 4-6 facilities are allowed by law to charge user fees. For the remaining facilities, we will then randomly sample levels 2 and 3. The numbers will be proportionate, targeting a maximum 20 facilities per county. For clients, we will randomly sample a minimum of 1600 clients exiting the health facilities per group, assuming a mean difference of 10% in client satisfaction between the two groups and a population variance of 55 across the groups using 80% power, 95% confidence level and a design effect of 3. To calculate the variance, we took an average of the outcome of the interest in the control and intervention (expected).^28^,^30^ We divide the 1600 clients equally among the selected facilities to achieve a minimum sample of 20 per facility as is recommended for cluster randomised trials.^28 30^ The following sample size calculation formula was used:

,$$n=\left(Z_{\alpha /2}+Z_{\beta \;}\right)sqrd\times 2\times \;\sigma^{2}\;/d^{2}$$

where Z_α/2_=1.96 (5% significance), Z_β_=0.84 (80% power), σ^2^=population variance of 59 (SD of 19 per group) and d=mean difference of 8% between the two groups.

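### The cross-sectional secondary design is said to ensure that effects can be measured, but it can give only an association, and its comparator is not pinned down

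*Protocol article*

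**What the plan says.** The section Secondary study design foresees that the counties chosen for intervention may not introduce the reform within the study's 12 months. Its response is: "we will sample four additional intervention counties that have already implemented autonomy reforms". The analysis is then described: "We will use a cross-sectional study design comparing these four counties that are already implementing autonomy". Their comparator is named as counties lacking autonomy, glossed in brackets as the controls. A second purpose follows, for the case in which follow-up is too short to show anything in counties that have only begun roll-out: "This design will also ensure that we can measure effects in the event the time of the study is not sufficient".

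The same section adds a second design, an interrupted time series on monthly routine (DHIS) indicators, 24 months before and 24 months after introduction in each county.

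On the counties, Study population gives "4 implementing autonomy reforms, 4 planning to implement and 4 controls". Sample size and sampling says how they were chosen: "we will purposively sample four counties already implementing autonomy reforms, four planning to implement the intervention and four not implementing as control". Autonomy reforms in Kenya explains that some counties had come to see a need for autonomy and granted it through their own laws or policies, while many others kept it limited.

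On earlier evidence, the Background says that "the few quantitative studies in this area are cross-sectional, presenting attribution challenges".

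**The concern.** The protocol justifies itself partly by the weakness of earlier cross-sectional work, then offers a cross-sectional comparison as a guarantee that effects can be measured. Nothing in the article explains why attribution would succeed here.

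If roll-out stalls, this comparison is the only between-group evidence described for readiness, the primary outcome. Differences between counties that adopted early and counties that did not could then be reported to policymakers as results of the reform, at a time when the new law obliges every county to adopt it.

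A second weakness is that the comparator is not fixed. Counties without autonomy and control counties are treated as the same set. They are not the same if the planning counties have not yet converted, and their facilities and clients are surveyed in any case.

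**Working it through.** **1. What the design contains**

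| Feature | Protocol article | Consequence |
|---|---|---|
| Adopting counties | Reform in place before sampling (Secondary study design) | No pre-reform survey of readiness or satisfaction |
| How they came to adopt | By county decision (Autonomy reforms in Kenya) | Exposure is self-selected |
| How counties were sampled | Purposively, in all groups (Sample size and sampling) | Sampling does not balance the groups |
| Context | Reform effects are expected to depend on institutional, socioeconomic and geographic factors (theory of change section) | Such factors may also differ between adopters and others |
| Time series | Routine DHIS indicators | Pre-reform data, but not on surveyed readiness or satisfaction |

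Readiness comes from the facility questionnaire and satisfaction from exit interviews (Data collection). The time series can inform utilisation but cannot replace the cross-section for these two outcomes.

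**2. The plan's own figure**

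Inputs from the text of Sample size and sampling: difference 10, variance 400 (SD 20), 80% power, 95% confidence, design effect 1.2.

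- n = 2 × (1.96 + 0.84)² × 400 / 10² = 62.72
- 62.72 × 1.2 = 75.3, so 76 facilities per group

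The stated 80 is 4 counties × 20 facilities, a conservative rounding (power 82.3%). It is not in dispute here.

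**3. Precision with 4 or 8 comparator counties (illustration)**

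Assumptions: 20 facilities per county, equal county variances, and the design effect of 1.2 read as county clustering, which implies an intracluster correlation of 0.2/19 = 0.0105.

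- Variance of a county mean = 400 × 1.2 / 20 = 24
- 4 v 4: SE = √(24 × (1/4 + 1/4)) = 3.46
- 4 v 8: SE = √(24 × (1/4 + 1/8)) = 3.00
- Ratio = √(0.375/0.5) = 0.866, about 13% smaller

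The ratio does not depend on the intracluster correlation, but the SEs do. At assumed values of 0.05, 0.10 and 0.20 they are 4.42, 5.39 and 6.93 (4 v 4), and 3.82, 4.66 and 6.00 (4 v 8).

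**4. What extra counties do to confounding**

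Suppose that the reform has no effect and that a readiness gap b existed beforehand. The chance of a two-sided significant result is 1 − Φ(1.96 − b/SE) + Φ(−1.96 − b/SE). The values of b are assumptions; the document gives none. The SEs are 3.46 and 3.00.

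| Pre-existing gap (points) | 4 v 4 | 4 v 8 |
|---|---|---|
| 3 | 13.9% | 17.0% |
| 5 | 30.3% | 38.5% |
| 8 | 63.7% | 76.0% |
| 10 | 82.3% | 91.5% |

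If the same gap applies to both comparators, the larger one makes a false claim more likely, because the bias stays and the SE shrinks.

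**5. When the planning counties qualify as comparators**

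- Baseline: they have no autonomy, so they qualify.
- Endline, not converted: they still have none, so they qualify.
- Endline, roll-out begun: they do not qualify. This is the situation that the quoted assurance addresses.

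**The case against.** The strongest defence is that the design is labelled secondary and contingent, and that the disputed sentence has a sensible purpose. Established adopters have had longer exposure, so they may show differences that 12 months in new adopters would not. That stands as a reason to survey them. It does not turn a difference between counties into an effect of the reform.

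The time series is also a fair reply to any suggestion that the contingency plans lack pre-reform data. It has 24 months of them, and the protocol does not rank the two secondary designs. The concern is therefore limited to the cross-section and to the outcomes that the time series does not reach.

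A reader might infer that the plan excludes the four planning counties from the comparison. The group labels and Table 1 make that the natural reading, but the text does not state it: unconverted counties also literally lack autonomy. The supportable point is that the comparator and the survey round are ambiguous.

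A reader might also infer that the planning counties are the best match for the adopters. Nothing in the article shows this. They too were chosen purposively, and the new law applies to all counties. Pooling them with the controls may add heterogeneity.

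Finally, adjustment methods for the cross-section may be in the full protocol or analysis plan. Their absence from an article is not a fault and is not counted as one here. The fault is the assurance that the article gives.

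**Conclusion.** The assurance claims a property that the design lacks. A post-only comparison of self-selected, purposively sampled adopters with counties lacking autonomy estimates an association, and the Background recognises this limitation in others' work. This conclusion rests on the text alone and needs no numerical assumption.

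The size of the resulting bias cannot be derived from the document. The gaps of 3 to 10 points in the working are assumptions that show sensitivity, and they are not estimates. The 13% precision gain is correct under equal county variances but concerns a different matter from confounding, so it should not be taken as a remedy. The essential change is to the stated conclusion; fixing the comparator is a useful addition.

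The documents do not support the stronger claims that the planning counties have no part in this design, or that all of the contingency plans lack pre-reform data.

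**What to change.** 1. In Secondary study design, replace the assurance with a statement that the cross-sectional comparison estimates an adjusted association between established autonomy and the outcome, and will not be reported as the effect of the reform.
2. Define the comparator by autonomy status at a named survey round. Use the four control counties as the stated comparator. Show as an additional comparison the planning counties' baseline data, and their endline data only for counties that have not converted by then.
3. Say that the time series covers routine indicators only, so that readiness and client satisfaction rest on the surveys.

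The cost is a less favourable claim for this design and a little more analysis. Items 1 and 3 are wording. Item 2 uses facilities and clients that are surveyed anyway.
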